**Physical assessments:**			
Sit-to-stand	x	x	x
Push up test			
Timed up-and-go			
Balance			
2-min step test			
Sit and reach			
**Questionnaires:**			
Physical activity self-efficacy (PASES survey)	x	x	x
Physical activity level (Godin's LSI)			
Quality of life (EQ5D5L)			
Self-reported fitness (IFIS)			
Fatigue (PedsQL-FMS)			
Implementation outcomes (e.g. Acceptability, RE-AIM framework)			x

### Physical fitness outcomes

2.5

Physical fitness assessments will be conducted online using Microsoft Teams at each time point, and will take approximately 20–30 ​min, with results recorded in REDCap. All assessors will be trained in the assessment protocol, with the lead researcher having paediatric exercise oncology experience. Assessors will send videos of each assessment prior to the session, and then explain and demonstrate each assessment prior to the participants’ attempt. The researcher will record the results and supervise participants, in addition to having a parent or guardian supervising them in person, unless mutually agreed that parent supervision is not required (for adolescent participants). The physical fitness assessments (Table 1) include the following validated assessments.

#### Sit to stand

2.5.1

The 30 ​s sit-to-stand (STS) test is a measure of lower body strength, measures the number of sit-to-stand repetitions completed over a 30 ​s period [28], which the researcher will count. The higher number of sit-to-stands performed is indicative of greater lower body strength.

#### Push up

2.5.2

A 30 ​s push up test will be used to measure upper body strength, with the total number performed measured [29]. Participants will perform the same type of push up at all assessments, which will be a full (toes on floor) or half (knees on the floor) push up.

#### Timed up and go

2.5.3

Timed up and go (TUG) test assesses physical function, by recording the time a patient needs to get up from a chair, walk 3 ​m, turn around, walk back, and sit down again [30]. Participants will be provided with a pre-cut 3-m rope. This is measured in seconds with a handheld stopwatch, with participants performing the TUG two times, with the mean of these measurements then calculated.

#### Balance

2.5.4

A single leg balance test will be conducted to assess static balance in two conditions: eyes open and eyes closed [31]. The participant will be placed standing near a wall, with arms crossed, and legs parallel to each other on a flat surface, with a parent/guardian standing beside them. Both sides will be assessed up to two times, with the highest score taken. Participants stop the test if their arms come off the crossed position, if their legs touch each other or begin to flail, or if they reach the maximum of 30 ​s.

#### 2-Min step test

2.5.5

This is a sub-maximal test of cardiovascular fitness [32]. Participants will stand with their right leg facing the camera, and instructed to march on the spot for 2 ​min. The participant is instructed to raise their knee height, so the thigh becomes parallel to the floor when marching. When the test starts, participants begin marching on the spot. The researcher will count the number of steps completed within the 2-min time frame on the leg facing the camera. Participants will report their rate of perceived exertion (RPE; 1–10) [33] after the assessment has been completed.

#### Sit and reach

2.5.6

Sit and reach test is a measure of flexibility of the lower back and hamstring muscles, which has been extensively used and validated in childhood populations [34]. This test involves sitting on the floor with legs stretched out straight ahead. The participant holds that position for at least 2 ​s while the distance is recorded by their parent/guardian. Touching the toes equals the baseline (0 ​cm), with any performance past the toes indicating a positive score in cm, and not reaching the toes indicates a negative score in cm. Participants will be provided with a ruler to measure the distance from the toes.

### Patient-reported outcomes

2.6

Participants will complete questionnaires online in REDCap at baseline (T0), post-intervention (T1), and follow-up (T2). All included questionnaires are validated for completion by children of 5 years of age (except the EQ-5D-Y-5L which is from 8 years). Parents will be encouraged to assist their children in completing the questionnaires if required. Parents can also complete the questionnaires as proxy for their child particularly in the cases of cognitive dysfunction or unwillingness from participant.

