### Outcome measures

2.4

Outcome measures are presented in Table 1, and will be completed at three time points: (1) baseline (T0; week 0); (2) post-intervention (T1; week 12); and (3) follow-up (T2; week 24). Physical assessments are conducted online using Microsoft Teams by an AEP in the research team. Patient-reported outcomes (PROs) questionnaires will be emailed to each participant's parent/guardian at all time points via REDCap. Accelerometers will be mailed to participants to be worn for 5-days at the baseline (T0) and post-intervention (T1) timepoints.

**Table 1 tbl1:** Summary of study timepoints and procedures.

	Baseline (Week 0)	Post-intervention (Week 12)	Follow-Up (Week 24)
**Accelerometer:** Physical activity level (wrist-worn accelerometer for 5-days)	x	x	

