#### Self-efficacy

2.6.1

Physical activity self-efficacy will be measured via 8 items using the Physical Activity Self–Efficacy Scale (PASES), which has been validated for use among children and adolescents [35].

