### Education

2.9

Within each of the five AEP intervention consultations, there will be a discussion incorporating an educational topic about the role of exercise in childhood cancer. This will be delivered using video and written information resources and discussions on the topic which will be addressed to the parent, with age-appropriate language tailoring to the participant. This will facilitate further learning on behaviour change techniques and key exercise principles in cancer care. The education topics include (1) Principles of Exercise and Cancer, (2) Graded exercise: how to progress and regress, (3) Activity pacing for fatigue, (4) Digital technology and local programs, and (5) a topic chosen by participant from: managing peripheral neuropathy, social support, long-term maintenance, and self-monitoring physical activity. These education topics were developed by engaging with consumer families, and designed to build self-efficacy to equip participants with the behaviour change techniques to apply in their daily life, in line with the study primary aim. Specific skills learnt include self-monitoring, barrier management, planning, goal setting, growing social support, and building confidence and belief in their own ability to be physically active.

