### Assessing implementation: the reach, effectiveness, adoption, implementation, and maintenance (RE-AIM) framework

2.11

The reach, effectiveness, adoption, implementation, and maintenance (RE-AIM) framework will be used to evaluate the implementation of the MERRIER study into a community organisations usual operations from individual (i.e., survivors and families) and organisational levels [46]. Reach will be measured by the calculating the proportion and characteristics of individuals who were eligible and able participate, as well the proportion excluded and reasons for exclusion. Effectiveness measures of the co-primary outcomes (self-efficacy and objectively measured moderate-vigorous physical activity), and secondary outcomes (e.g., patient-reported outcomes and physical assessments) for group changes will be conducted between baseline (T0) and post-intervention (T1). Adoption will be measured by calculating the number of enrolled and completed participants by the total eligible, while qualitative interviews with research staff will be conducted iteratively to understand reasons for non-recruitment and drop-out mid-way through recruitment. Implementation will be measured by calculating the adherence (percentage of prescribed exercises completed) and compliance (percentage of exercise intervention consultations completed, and number of participants who complete >70 ​% of their prescribed exercises using the Physitrack exercise software), and listing adaptations made to the intervention during the study. Maintenance will be a measure of the co-primary and secondary outcomes at post-intervention (T1) and 24-week follow-up (T2) (i.e. >60 ​% of participants report a self-efficacy score and physical activity minutes (using self-report) equal to or higher than their baseline score at the 24-week follow-up (T2)). Fidelity checks will be carried out to ensure consistency and safety in the delivery of the online exercise intervention. Consultations will be recorded using Microsoft Teams and stored on a secure password-protected cloud-based network at The University of Sydney for quality assurance. Ten percent of exercise consultations will be randomly reviewed to observe and improve program delivery.

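### The proxy rule covers the co-primary self-efficacy scale and does not hold the respondent constant, so one child's T0–T1 comparison can mix child and parent ratings

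*Protocol article*

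**What the plan says.** Section 2.6 (Patient-reported outcomes) makes the child the default respondent and adds two relaxations. The first is help: "Parents will be encouraged to assist their children in completing the questionnaires if required". The second is substitution: "Parents can also complete the questionnaires as proxy for their child particularly in the cases of cognitive dysfunction or unwillingness from participant". The word introducing the two reasons makes them examples rather than limits.

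PASES falls under this rule. Section 2.6.1 describes it as the "Physical Activity Self–Efficacy Scale (PASES), which has been validated for use among children and adolescents", and no parent version is mentioned. Section 2.11 gives its status: "Effectiveness measures of the co-primary outcomes (self-efficacy and objectively measured moderate-vigorous physical activity" are compared between T0 and T1. The same section defines maintenance partly by whether each participant's self-efficacy at T2 has at least held its baseline level, with a target of more than 60% of participants.

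Three further statements bear on who answers and what they know:
- Section 2.4: "questionnaires will be emailed to each participant's parent/guardian at all time points via REDCap".
- Section 2.9: in the intervention consultations the education consists of resources and "discussions on the topic which will be addressed to the parent, with age-appropriate language tailoring to the participant". Its stated purpose is to build self-efficacy.
- Section 2.10: controls receive emailed resources and are offered the programme only after T2.

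**The concern.** Self-efficacy is the child's confidence in his or her own ability. A parent's estimate of that confidence is a different measurement, and the two need not agree. Where the respondent is the same at every visit, any constant gap between parent and child cancels from the change. Where the respondent changes, the gap enters the change as if the child's confidence had moved.

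Unwillingness can come and go between visits, so the rule as written can produce such changes. If they occur more often in one arm, part of the arm difference on a co-primary outcome reflects who answered. The maintenance criterion is exposed even without an arm difference, because it compares each participant with his or her own baseline.

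This must be settled before scores are collected. If the respondent is not recorded, no later analysis can recover it.

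**Working it through.** **The plan's own figure.** The article gives no figure for PASES or for the expected share of proxies. Its one calculation (section 2.13) concerns the accelerometer: 10 min/day difference, SD 11, 90% power, p < 0.05. Two-sided, with 1:1 allocation:

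n per arm = 2 × (1.960 + 1.282)² × (11/10)² = 2 × 10.51 × 1.21 ≈ 25.4, rounded up to 26, so 52 in total.

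This matches the stated 52. It shows nothing about self-efficacy, but it sets the scale of the trial: 60 enrolled less 15% leaves 51, or about 25.5 per arm.

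**Structure of the bias.** Let p_I and p_C be the shares of children in the intervention and control arms whose respondent switches from child at T0 to parent at T1. Let d be the mean parent-minus-child gap in SD units, taken as the same in both arms. With no true effect:

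bias in the arm contrast = (p_I − p_C) × d = f × d

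- If p_I = p_C, then f = 0 and the contrast is unbiased; the mixture only adds variance.
- If f ≠ 0, the contrast is biased. The direction depends on the signs of f and d, and the documents give neither.

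**Illustration.** The values of f and d are assumptions. The standard error of the difference in SD units is √(2/25.5) = 0.280, and the test is two-sided at 5% under a normal approximation:

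| f | d (SD) | Bias (SD) | Bias / SE | Type I error |
|---|---|---|---|---|
| 10 points | 0.3 | 0.03 | 0.11 | 5.1% |
| 20 points | 0.5 | 0.10 | 0.36 | 6.5% |

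For the second row: Φ(0.36 − 1.96) + Φ(−0.36 − 1.96) ≈ 0.055 + 0.010 = 0.065. The lower case is negligible. The upper case is modest but avoidable.

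**Maintenance criterion.** Here the quantity is the proportion of participants whose T2 score is at or above baseline. A child who switches to a parent respondent has d added to the T2-minus-baseline difference. If d is positive, more switched children pass; if negative, fewer do. No second arm cancels this, so equal switching rates give no protection. The documents supply no distribution from which to size it.

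**The case against.** **Switching is inferred.** No sentence says that the respondent may change; the article is only silent on consistency. The stated default is the child, and a condensed article may leave such handling to the full protocol or the data-capture build. This stands as a limit on how firmly the point can be put. It does not remove the point, because the open-ended permission is itself stated text, it covers a co-primary, and nothing shown restrains it.

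**The coached parent.** A reader might infer that an unblinded parent, coached by the programme, will replace the child at T1 and push the score up. The documents do not support that. Families' knowledge of allocation follows from the design (telehealth programme against emailed resources), and it applies to the child too. The child is also taught and exercises with the exercise physiologist at each consultation. Nothing shows that a parent's rating would be more biased than the child's, or in which direction.

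**Larger bias figures.** One could suppose 30% proxies at T1, with intervention parents rating 0.5 SD higher, and obtain 0.30 × 0.5 = 0.15 SD. That describes parental optimism that differs by arm. It could arise with the same parent answering at both visits, and fixing the respondent would not remove it. It is not evidence for this point.

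**Proxies serve inclusion.** Sound. The age range is 5–18, brain tumours are a randomisation stratum, and cognitive dysfunction is the first reason named for a proxy. Removing all proxies from the main analysis could lose many scores (at an assumed 30%, 0.30 × 51 ≈ 15). Setting unwilling children to missing could introduce selection if unwillingness is related to arm. The remedy should therefore keep consistent proxies.

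The push-up rule in section 2.5.2, which holds the variant constant across assessments, shows that the principle is recognised, but a performance test is only a loose parallel.

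**Conclusion.** The point holds in a limited form. As written, section 2.6 permits a parent to answer the co-primary PASES for open-ended reasons and does not hold the respondent constant, so a child's T0–T1 or T2-versus-baseline comparison can mix two kinds of rating. Similar switching in both arms mainly costs precision in the arm contrast but can still move the maintenance proportion. Differential switching biases the contrast, by about 0.03 to 0.10 SD over the assumed range, with type I error of 5.1% to 6.5% at about 25.5 completers per arm.

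Those sizes rest on assumed switching rates and an assumed parent–child gap. The documents establish neither, and they do not show that switching will differ by arm. The accelerometer co-primary, which alone drives the sample size, is untouched, so the point bears on one half of aim 1. It merits correction because the remedy is nearly free and cannot be applied afterwards.

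**What to change.** In section 2.6, add that:
1. the respondent for each child (the child, or a proxy for a documented reason) is set at T0, before randomisation; section 2.3 already places randomisation after the baseline questionnaires;
2. the same respondent answers at T1 and T2;
3. the actual respondent is recorded in REDCap at every visit, so that any departure is flagged.

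In the analysis, keep children with a consistent proxy in the main PASES comparison. Add a sensitivity analysis limited to scores that are child-reported and have the same respondent throughout.

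The cost is one REDCap field, a few sentences, and possibly a few PASES scores that are missing or flagged. Differential optimism among consistent proxies would remain; the sensitivity analysis shows whether the result depends on them.

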#### Self-efficacy

2.6.1

Physical activity self-efficacy will be measured via 8 items using the Physical Activity Self–Efficacy Scale (PASES), which has been validated for use among children and adolescents [35].

#### Physical activity

2.6.2

Physical activity levels will be self-reported using Godin's Leisure Score Index, which is a four-item self-report questionnaire [36]. Three questions are stratified by intensity (low, moderate, and vigorous), and will be tallied for a global weekly score. We will ask participants for average minutes to calculate minutes per week for each intensity. This questionnaire has shown good reliability/validity in children and adolescents without cancer, with test-retest co-efficient ​= ​0.84 and previously used with childhood cancer survivors [37].

#### Fitness

2.6.3

The International Fitness Scale (IFIS) developed by Ortega et al. (2011) assesses self-perceived fitness in adolescents, including cardiovascular, sprinting, muscle, flexibility and overall fitness, with answers using a 5-point Likert-scale [38].

#### Quality of life

2.6.4

Quality of life will be measured using the EQ-5D-Y-5L, which is measure of health-related quality of life (HRQoL), and includes 5 items on a 5-point Likert scale relating to different domains of HRQoL and validated for use in children [39]. Additionally, we will use the EQ VAS, which a single measure asking participants to ‘rate your health between 0 and 100'.

#### Fatigue

2.6.5

The PedsQL™ 3.0 Multidimensional Fatigue Scale™ (PedsQL-FMS) is a questionnaire consisting of 18 items describing symptoms of cancer-related fatigue. Each item is rated for how frequently it is a problem on a 5-point scale from 0 “almost never” to 4 “almost always”.

### Objective physical activity levels

2.7

Average daily minutes of moderate-vigorous physical activity will be objectively measured using an Axivity AX3 accelerometer. The Axivity AX3 accelerometer is a research-grade waterproof wrist accelerometer that records continuous daily activity and captures acceleration along three axes (x, y, and z) with a sample frequency of 100 ​Hz. It shows good validity and accuracy at both wrist locations (ICC of 0.91 for comparison of left and wright wrists) [40], and validated with other research grade accelerometers with an ICC of 0.95 [41]. Participants will be instructed to attach the Axivity AX3 accelerometer on their non-dominant wrist for 5 consecutive days (including two weekend days and evenings). To be included for weekly physical activity calculations, at least four valid days are required. Valid days are defined as wearing the accelerometer for at least 10 ​h/day [40] with non-wear time being defined as not wearing the accelerometer for 60 consecutive minutes [41]. Accelerometer data will be collected at the start and end of the intervention. Participants will be provided with instruction on how to wear the accelerometer and will be provided with postage paid return envelopes for baseline (T0) and post-intervention (T1). Once returned to the researchers, participant data will be immediately downloaded onto a password protected computer.

### Exercise intervention

2.8

The five exercise consultations are conducted online using Microsoft teams, and the exercise prescription is delivered remotely to participants using Physitrack (Physitrack Limited) exercise prescription software (available to participants as a website or digital application). Within two weeks of the baseline assessment, participants randomized to the intervention will receive the first of five telehealth consultations with an AEP (Fig. 1) over 3 months to develop and go through an exercise program individualised to their needs, physical activity levels, barriers, preferences and goals. The program will be designed with the purpose of participants utilising themselves, and/or with their family, peers, community sport and at school. Participants will be mailed simple exercise equipment to use at home for their program based on their preferences and needs such as resistance bands, skipping ropes and provided with a $50 (AUD) voucher to use on sport or physical activity equipment. The MERRIER exercise intervention is guided by exercise guidelines in childhood cancer [11], previous research (e.g. PICASSO Study [20] and the CanMOVE study which also adopts a flexible exercise prescription approach during the treatment phase for childhood cancer [42]), as well as the RePlay theoretical model for structured active play [43], and was co-designed with oncology health professionals, and childhood cancer survivors and their parents. The number of supervised consultations in the study (five) was selected to be in line with the number of government subsidised (Medicare) sessions with an AEP or physiotherapist available each year to Australians with a chronic condition.

During each consultation with the AEP, participants will discuss any challenges with the program, and adjustments will be made. The second component of each consultation is completing each prescribed exercise together, allowing for technique adjustments and questions. Where required, participants will be offered strategies on increasing their physical activity participation in line with the paediatric oncology exercise guidelines [11]. Physical activity programs will be structured and individualised based on the framework in Table 2.

**Table 2 tbl2:** Framework for structure of exercise physiology consultations and factors for exercise prescription.

Exercise Guidelines	**Duration:** Education on paediatric oncology physical activity guidelines (“Move when you can”) [11]
	**Intensity:**Education on how to interpret exercise intensity using the modified borg rate of perceived exertion 1–10 intensity scale [33]. Education on light (1–3/10), moderate (4–5/10) and vigorous exercise intensities (≥6/10), and how to achieve these.
Type of exercise	**Aerobic, resistance, stretching, balance)**: Each program will include a component of age-appropriate aerobic, resistance, and stretching exercises, with balance exercises prescribed as needed. Exercises will be age-specific (e.g. games for young children, gym/structured programs for adolescence, sport teams for all. The exercises can be recommended do be done as an individual, or with siblings, parents, or friends. The exercise program will be provided using the physitrack software. Participants may also be recommended to use technology to promote adherence such as pedometers, digital exercise applications, or age-appropriate online videos.
Preferences based on enjoyment and goals	Exercises will be prioritised based on preferences and enjoyment (i.e. sport, play-based, dancing, games-based, cycling, walking, swimming, team sports) Discuss short and long-term goals (e.g. number of daily steps or minutes, assessment performance goals, return to sport or activity, reducing symptoms). If goal is not achieved, discuss why not and a formulate contingency plan.
Education	Each appointment will include an educational component with videos and discussion, which include: 1. Principles of exercise and cancer 2. Graded exercise: How to progress and regress 3. Activity pacing for fatigue 4. *Topic chosen by participant from*: managing peripheral neuropathy, social support, long-term maintenance, self-monitoring physical activity 5. Digital technology and local programs
Referral	At the conclusion of the intervention, the study team will recommend a local exercise professional (e.g. accredited exercise physiologist, physiotherapist, or community sport program) who can also assist with delivering a face-to-face exercise program locally, if they choose to. Participants will be encouraged to share their prescribed program with local health professionals and their school teachers, so their teachers are informed on any exercise considerations and any contraindications, who will be permitted to communicate with the research team for information regarding the program.

An example of the exercise program parameters is presented in Table 3, and further detail for each consultation is presented in Supplementary File 1. Each online consultation in the intervention group will be 45–60 ​min in duration. This is broken down into a 20-min discussion including: goal setting, discussing the prescribed physical activity program, and providing education. Following will be a 30-min supervised exercise session, which includes: (1) 5 ​min warm-up; (2) 20 ​min of exercise training consisting of strength/resistance, balance, and aerobic activities, and (3) 5 ​min cool-down consisting of full-body stretching. The AEP demonstrates each exercise, tailoring to address participants’ needs including exercise progressions (e.g. push-ups from wall to floor) or regressions (e.g. push-ups from floor to wall).

**Table 3 tbl3:** Example of exercise program parameters, which may vary based on baseline level of physical function, fitness and exercise history.

Video Consult #	Consultation 1	Consultation 2	Consultation 3	Consultation 4	Consultation 5
Week	1	2 to 3	4 to 6	7 to 9	10 to 12
Theme	Adaptation	Individualisation	Progressive overload		Transition
Contents	Warm up, teaching about movements and equipment	Tailoring exercises to needs of individual, motor skills, strength, fitness	Strength, fitness, motor skills		Strength, fitness, motor skills
Resistance exercises	Body weight only (E.g. bridges)	Body weight only (e.g. knee push ups)	Introduce light resistance bands, hand weights or jumping	Combination of resistance exercise types	
Aerobic exercises	E.g. Dancing, bike riding, ball games	Introduction to circuit training	Introduction of vigorous intensity bouts		
Other exercises (e.g. introduce balance exercises as needed if balance/stability is an issue)	Static	Static	Dynamic	Eyes open/closed	Challenging
Sessions per week	2	2	3	3	3
Total number of exercises	3	3 to 4	4 to 5	5	5 to 6
Minutes per session	15	20	25 to 30	35	40
Rest time (sec)	90	90	75	60	60
Rating of perceived exertion (/10)	4	5	6	6 to 7	6 to 8

